### Quality control

2.8

In order to guarantee the quality of trial, all investigators are asked to attend special training includes how to fill in the Case Report Form, how to record adverse reactions, how to teach the patients to take medicine, and other details of this trial.

## Discussion

3

Fatigue, as a concurrent symptom of UC, is frequently overlooked due to its intricate and subjective nature, posing challenges for medical staff. Nevertheless, fatigue not only exacerbates UC symptoms but also significantly impacts patients' quality of life. Clinicians should prioritize attention to the fatigue symptoms experienced by patients with UC to ensure comprehensive and effective care [23].

The etiology of fatigue in UC remains unclear. Drawing insights from research on fatigue mechanisms in other diseases, it is proposed that fatigue may result from various factors, primarily associated with the activation of the immune system, disease activity, and the release of pro-inflammatory factors [8,24,25]. Dysbiosis of gut microflora, a known contributor to gut inflammation, is now implicated in regulating fatigue through the gut–brain axis, which involves two-way communication between the gastrointestinal tract and central nervous system and gut microbes and the immune system [26]. Tryptophan metabolites [27] and polyphenol metabolites [28] have shown promise in alleviating fatigue. A prospective study suggested that microbiome- and metabolite-directed therapies reduce fatigue and depression in patients with IBD [29].

The multifaceted nature of fatigue in UC suggests the existence of different subtypes, requiring tailored intervention measures.

Despite advancements in clinical research, addressing nutrient deficiencies and using immunomodulators or biological agents to reduce systemic inflammation may not entirely alleviate UC fatigue. Studies indicate that biopharmaceuticals and small molecular drugs used for IBD, including ustekinumab, infliximab, natalizumab, tofacitinib, and upatinib, have limited efficacy in relieving fatigue [30]. Even selective JAK1 inhibitors like upatinib, while showing a significant effect on UC fatigue through long-term maintenance, lack clarity on the extent of their impact [31]. Despite the potential connection between nutrient deficiency and fatigue, there is no evidence supporting fatigue improvement in the long-term maintenance of 300 mg thiamine therapy [32], excessive use of vitamin B12 [33], and maltol iron [34] supplementation in IBD fatigue.

TCM exhibits unique advantages in combating fatigue by regulating gut microbes, protecting nerve centers, enhancing antioxidant enzyme activity, reducing metabolite accumulation, and influencing energy metabolism [35]. The JPQC prescription, designed to invigorate the spleen and replenish qi, primarily employs Qi-tonifying herbs to restore spleen Qi. Notably, Qi-tonifying herbs have demonstrated the ability to regulate intestinal flora, restoring diversity and balance [36]. Clinical studies have demonstrated that the combination of JPQC with mesalazine exerts a distinctive synergistic mechanism on the intestinal flora and metabolites of patients with ulcerative colitis (UC) by downregulating erysipelatoclostridium and decreasing the levels of 4-pyrimidine methanamine (hydrochloride), hydroxyprolyl-isoleucine, and L-glutamate. Notably, these three metabolites play a role in anti-inflammatory processes and contribute to enhanced amino acid metabolism [37]. The investigation into whether JPQC further influences UC with fatigue by regulating the disorder of intestinal flora and its metabolites presents an intriguing and crucial research topic.

The primary aim of our study is to explore the impact of JPQC on the intestinal flora and metabolites of patients with UC with spleen deficiency damp-heat type and fatigue. The study aims to investigate the clinical effects of JPQC on patients with UC with spleen deficiency and dampness-heat syndrome accompanied by fatigue, along with its regulatory mechanism on intestinal flora and metabolites. This research will contribute valuable insights into TCM's role in managing UC-related fatigue and may pave the way for novel therapeutic approaches.

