## Abstract

**Background:**

Ulcerative colitis (UC) is a chronic non-specific inflammatory intestinal disease, categoried under "dysentery" and "intestinal bleeding" in Traditional Chinese Medicine (TCM). Jianpi Qingchang decoction (JPQC) is a combination formula specifically designed for the treatment of UC. The primary objective of this study is to examine the clinical efficacy of JPQC in individuals diagnosed with UC who exhibit both spleen deficiency and dampness-heat syndrome, along with the presence of fatigue. The investigation will focus on assessing the impact of JPQC on the gut microbiota and metabolites in these patients, aiming to elucidate the regulatory mechanism that JPQC exerts on the gut microbiota and metabolites in the context of UC-related fatigue.

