**Methods:**

In this randomized clinical trial, 140 subjects diagnosed with UC will be recruited and randomized into two groups. They will receive either JPQC combined with mesalazine or mesalazine alone for 12 weeks. Follow-up visits will be conducted every four weeks, with a post-treatment visit scheduled at 6 months. The primary outcome measures include the Inflammatory bowel disease fatigue scale(IBD-F). Secondary efficacy indicators comprise the assessment of TCM syndrome and individual syndrome efficacy before and after treatment, Modified Mayo score, Simple clinical colitis activity index (SCCAI), as well as the Inflammatory Bowel Disease Questionnaire (IBDQ) for each group. The other outcomes are the Intestinal microbial diversity and non-targeted metabonomics, which will be measured at baseline and 12 weeks after randomization.

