### Mechanism outcomes

2.5

The procedure involves the detection and analysis of intestinal microbial diversity and non-targeted metabonomics. To conduct this, it is essential to collect freshly excreted feces, preferably from the first bowel movement in the morning. Approximately 2 g of the middle section of the feces should be carefully extracted and deposited into a sterile fecal collection tube. Two distinct fecal samples need to be collected sequentially, with detailed information such as name, sex, age, and sampling time noted for each specimen. These outcomes are measured before and after treatment.

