### Statistical analysis

2.7

Statistical analysis will be conducted using SPSS 24.0 software. Descriptive statistics for measurement data will include mean ± standard deviation ($\bar{X}$ ± S) for data conforming to normal distribution. Two independent samples t-tests will be employed for comparing means, and variance analysis for multi-sample comparisons. Nonparametric tests will be used for data not conforming to normal distribution. Counting data will be analyzed using the χ^2^ test, and rank sum test for rank data. Correlation analysis between two variables will use linear correlation for bivariate normal distribution data and Spearman rank correlation for non-bivariate normal distribution or graded data. A significance level of *P* < 0.05 will be considered statistically significant. The study will also provide statistical descriptions of adverse events, adverse reactions, dropout rates, and rejections during treatment.

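### The Discussion makes flora and metabolites the primary aim, contradicting the stated objective and primary outcome, and the step from flora to fatigue is not supported by the sampling and correlation method described

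*Protocol article*

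**What the plan says.** On rank, the protocol article says four things:

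- Abstract, Background: "The primary objective of this study is to examine the clinical efficacy of JPQC". The mechanism work follows as a further aim, not called primary: "aiming to elucidate the regulatory mechanism that JPQC exerts on the gut microbiota and metabolites in the context of UC-related fatigue".
- Abstract, Methods: IBD-F is the primary measure. After the secondary measures comes "The other outcomes are the Intestinal microbial diversity and non-targeted metabonomics".
- Section 2.4.1: the primary outcome is IBD-F. The stool work has its own section, 2.5, outside the primary and secondary outcomes.
- Section 3, Discussion: "The primary aim of our study is to explore the impact of JPQC on the intestinal flora and metabolites". The next sentence adds the clinical effects as an aim, without calling it primary. The paragraph before poses the mediation question as a research topic: "The investigation into whether JPQC further influences UC with fatigue by regulating the disorder of intestinal flora and its metabolites".

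On timing, section 2.5 says of the stool measurements "These outcomes are measured before and after treatment". The Abstract and Table 1 place them at baseline and week 12. Section 2.4.1 has IBD-F at baseline and weeks 4, 8 and 12, and Table 1 adds week 24.

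On analysis, section 2.7 gives one way of relating two variables: "Correlation analysis between two variables will use linear correlation for bivariate normal distribution data", with Spearman rank correlation otherwise. It does not say which pairs will be correlated, whether the arms are pooled, or whether anything is adjusted for.

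**The concern.** A trial should have one primary aim, matched to its primary outcome. If the flora and metabolites can also be called primary, the reader cannot tell which result decides the trial, and untargeted metabolomics with microbial diversity offers many features to choose from.

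The mechanism aim also asks for more than a comparison of flora between arms. It asks whether fatigue improves because the flora changes. Treatment is a common cause of both measures. A correlation across patients that ignores arm can therefore arise with no pathway between them, and would be easy to misread as the mechanism.

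**Working it through.** **Step 1. The statements on rank side by side.**

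| Place | What ranks first | Rank of flora and metabolites |
|---|---|---|
| Abstract, Background | Clinical efficacy | Further aim |
| Abstract, Methods | IBD-F | Other outcome |
| Sections 2.4.1 and 2.5 | IBD-F | Separate mechanism outcome |
| Section 3, Discussion | Flora and metabolites | Primary aim |

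The Discussion is alone against the other three.

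**Step 2. What the sampling times allow.** Stool is taken at weeks 0 and 12; IBD-F is taken at weeks 0, 4, 8, 12 and 24. The between-arm comparison of flora at week 12 is randomised and answers whether JPQC changes the flora. No stool sample falls between week 0 and week 12, so the data cannot show that flora changed before fatigue did during treatment. The week 24 IBD-F does follow the week 12 stool sample, but it does not order changes that were complete by week 12.

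**Step 3. What a pooled correlation would show with no link.** The article gives no figure for this analysis, so there is none to reproduce. From section 2.2.6 only the group sizes are used: 56 per arm, and 56 / (1 − 0.20) = 70 per arm with dropout added. Allocation is 1:1 (section 2.1). The treatment effects are assumptions, because the documents give none: JPQC shifts a stool feature and the fatigue score by the same d standard deviations, with zero correlation within each arm. The two variables may be read as week 12 values or as changes from baseline.

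With equal arms, a shift d adds d²/4 to each variance and d²/4 to the covariance, so the induced pooled correlation is

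r = (d²/4) / (1 + d²/4)

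- d = 0.3: 0.0225 / 1.0225 = 0.02
- d = 0.5: 0.0625 / 1.0625 = 0.06
- d = 0.8: 0.16 / 1.16 = 0.14
- d = 1.0: 0.25 / 1.25 = 0.20

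Opposite shifts (feature up, fatigue down) only change the sign of r.

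Simulating 5,000 trials per setting, with a Pearson test at P < 0.05, gave these proportions declared significant:

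| d | Pooled, 56 per arm | Pooled, 70 per arm | Given arm, 56 per arm | Given arm, 70 per arm |
|---|---|---|---|---|
| 0 | 4.8% | 4.4% | 4.8% | 4.2% |
| 0.3 | 5.8% | 5.4% | 5.2% | 4.4% |
| 0.5 | 8.9% | 10.3% | 4.8% | 4.5% |
| 0.8 | 30.9% | 35.9% | 4.8% | 5.3% |
| 1.0 | 57.9% | 67.4% | 4.3% | 4.9% |

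Correlation within one arm also stays near nominal, at 4.6–5.3% over all settings. The simulation covers only this artefact. It says nothing about timing or about other common causes.

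**The case against.** The strongest reply is that section 2.7 is a general list of methods. It does not say that flora will be correlated with IBD-F, that arms will be pooled, or that week 12 values rather than changes will be used. A mediation model or arm adjustment may sit in an analysis plan that is not shown, so its absence is not a fault in itself. This stands, and it makes the simulation conditional. A reader might infer that the article commits itself to calling treatment-induced co-movement a mechanism; the text does not go that far.

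Four further limits also stand:

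- **Size.** A reader might quote large error rates as the expected result. Fixing the feature shift at 1 SD and letting IBD-F shift by 0.5 to 1.0 SD gives 20% to 67%, but this needs both pooling and a large assumed shift. With equal shifts of 0.3–0.5 SD the inflation is small.
- **Timing.** It would be too strong to say the data have no time order, because Table 1 has IBD-F at week 24, after the last stool sample. The gap is the missing on-treatment stool sample before week 12.
- **Disease activity.** The Introduction links activity to fatigue (68.2% in active disease, 40.0% in remission) but does not say that activity drives it. It remains a plausible common cause, and correlation within arms would not remove it. Since the Discussion describes dysbiosis as contributing to gut inflammation, activity may also lie on the pathway from flora to fatigue.
- **Misuse.** A reader might infer that a null IBD-F result would be presented as success on the other aim. Nothing in the article shows that intent: IBD-F is the only named primary outcome, and the Discussion sentence itself speaks of exploring.

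None of this removes the contradiction in rank, and no later analysis can supply the missing stool samples.

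**Conclusion.** The contradiction over the primary aim is certain and rests on the text alone. That stool taken at weeks 0 and 12 cannot show flora changing ahead of fatigue during treatment is also certain.

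The false-positive argument is conditional. It holds if arms are pooled without adjustment, and its size depends on assumed shifts: about 6–9% at 0.3–0.5 SD, 31% at 0.8 SD and 58% at 1 SD with 56 per arm, against a nominal 5%. Conditioning on arm removes it.

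The randomised comparison of IBD-F is unaffected, and so is the randomised comparison of flora at week 12. Only the step from flora to fatigue lacks support, and it should not be reported as mechanism on this design.

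**What to change.** In section 3 (Discussion), name efficacy on IBD-F as the single primary aim, in line with the Abstract and section 2.4.1, and label the flora and metabolite work exploratory.

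In section 2.7, state that the week 0 to 12 change in each feature will be related to the change in IBD-F over the same period, adjusted for treatment arm or estimated within arm. Show adjustment for change in modified Mayo score only as a sensitivity analysis: it is measured after randomisation and may be part of the pathway. Table 1 already schedules that score at weeks 0 and 12.

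Word any flora–fatigue finding as association. Adjustment for arm removes the artefact shown above but does not establish time order or exclude other common causes.

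The cost is some rewording and a slightly larger model on data already planned, with no new visits, samples or patients. The downside is a more modest mechanistic claim and probably fewer significant correlations.

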## Ethics approval and consent to participate

We confirm that this trial will be conducted in accordance with the principles of the Declaration of Helsinki.

This study was approved by the Ethics Committee of Shanghai Hospital of Integrated Traditional Chinese and Western Medicine affiliated with Shanghai University of Traditional Chinese Medicine (2022-053-1). All participate will be required to sign written informed consent.

## Data Availability

No data was used for the research described in the article.
